## Independent Safety Review Team

A safety review team will review the progress and clinical and behavioral safety profile of this study while the study is ongoing. Safety data collected at each site will be reviewed rapidly by the investigators and CDC. The safety review team will convene at scheduled timepoints 6, 12, and 18 months following study initiation to examine the safety results of the trial and also focus on logistical issues such as accrual, retention, quality of clinical and laboratory data, and implications of results of external studies.

All serious adverse events (SAE) that are study related and unexpected will be provided to the safety review team at their regular safety reviews, and should any reportable SAEs occur, these will be reported to the safety review team at the same time as they are reported to the IRBs.

As TDF is a FDA-approved licensed drug that has already been evaluated in numerous previous safety studies, no formal stopping rules will be provided to the safety review team. However, ad-hoc meetings of the safety review team will be triggered by a) > two grade 4 adverse events of the same nature (e.g., two cases of hepatic failure) that are definitely or probably related to study product; b) > three grade 3 adverse events of the same nature that are definitely or probably related to study product. When reviewing the data at regularly scheduled time points or at ad-hoc reviews, the safety team will then be asked to make a clinical assessment to determine if the nature, frequency, and severity of adverse effects associated with a study regimen warrant the early termination of the study in the best interests of the participants.

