[Table 1: Study Schedule for HIV-1 Uninfected Participants (Immediate arm) (Part A) 210](#__RefHeading___Toc75597519)

[Table 2: Study Schedule for HIV-1 Uninfected Participants (Delayed arm) (Part A) 211](#__RefHeading___Toc75597520)

[Table 3: Study Schedule for HIV-1 Infected Participants (Part B) 212](#__RefHeading___Toc75597521)

[Appendix 4 FLIP CHART 213](#__RefHeading___Toc75597522)

[Appendix 5 STUDY INFORMED CONSENT 238](#__RefHeading___Toc75597523)

[Appendix 6 COMPREHENSION ASSESSMENT 250](#__RefHeading___Toc75597524)

[Appendix 7 TOXICITY SCALES 255](#__RefHeading___Toc75597525)

[Table 1: NIAID Toxicity Scale 255](#__RefHeading___Toc75597526)

[Table 2: GILEAD Toxicity Scale 269](#__RefHeading___Toc75597527)

[Appendix 8 TOXICITY ALGORITHMS 274](#__RefHeading___Toc75597528)

[Table 1: Management of Clinical and Laboratory Adverse Events (Except Creatinine) 274](#__RefHeading___Toc75597529)

[Table 2: Management of Creatinine Elevations 275](#__RefHeading___Toc75597530)

[Appendix 9 COUNSELING ASSESSMENT 276](#__RefHeading___Toc75597531)

[Appendix 10 CASE REPORT FORMS (CRF) 277](#__RefHeading___Toc75597532)

PROTOCOL SYNOPSIS

| Study Title: | Phase II Extended Safety Study of Tenofovir Disoproxil Fumarate (TDF) for Prevention of HIV among HIV-1 Negative Men |
| --- | --- |
| Study Sites: | AIDS Research Consortium of Atlanta (ARCA), Atlanta, GA  San Francisco Department of Public Health (SFDPH), San Francisco, CA Fenway Community Health (FCH), Boston, MA |
| Objectives: | Primary Objective:  To determine the clinical and behavioral safety and tolerability of oral daily TDF use as pre-exposure prophylaxis (PrEP) to prevent HIV infection in uninfected men.  Secondary Objectives:  To describe the number of HIV infections and to evaluate whether administration of oral TDF affects the genetic characteristics of HIV-1 breakthrough viruses  To assess social and behavioral effects associated with participation in this safety trial  To evaluate participants’ adherence with daily TDF |
| Design: | Phase II, double blind, placebo-controlled, equal (1:1:1:1) randomization |
| Population: | HIV negative men who have sex with men (MSM) |
| Stratification: | By site |
| Sample Size: | 400 HIV negative MSM |

| Duration of Study: | 24 months for HIV negative MSM, 12 months following HIV diagnosis for MSM who become infected while participating in the study |
| --- | --- |

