| Randomization  R  A  N  D  O  M  I  Z  E  Daily TDF  Daily Placebo  No treatment for 9 months, then daily TDF  No treatment for 9 months, then daily Placebo  Site B  Site A  Site C |  |
| Enrollment: | Over 24 months |
| Main eligibility criteria: | Healthy, HIV-1 negative MSM who reported anal intercourse in the last 12 months |
| Study procedures/frequency: | Physical examinations, behavioral risk assessments, and laboratory analyses at screening, baseline, months 1, 3 and then every 3 months through 24 months of study. |
| Test product, dose, and mode of administration: | TDF 300 mg po QD. |
| Criteria for Evaluation | Safety  Clinical and laboratory adverse events  Risk behavior change  Adherence to study drug  HIV antiretroviral resistance |
| Statistical Methods | The primary endpoints are to assess the safety and tolerability of TDF as determined by the proportion of participants with grade 3 or 4 abnormalities (clinical adverse events and laboratory toxicities occurring after treatment initiation), the difference in reported risk behavior between the immediate and delayed treatment arms, and overall rates of adherence. Intent-to-treat analysis will be used. |

GLOSSARY OF ABBREVIATIONS AND DEFINITION OF TERMS

| 3TC | lamivudine, Epivir® |
| --- | --- |
| 3TC/AZT | lamivudine/zidovudine, Combivir® |
| ACASI | audio-computer administered interview |
| AE | adverse event |
| AIDS | acquired immunodefienciency syndrome |
| ALT (SGPT) | alanine aminotransferase |
| AST (SGOT) | aspartate aminotransferase |
| ART | antiretroviral therapy |
| BUN | blood urea nitrogen |
| CAB | community advisory board |
| CBC | complete blood count |
| CBO | community based organization |
| CK | creatine kinase |
| CLIA | clinical laboratory improvement amendments |
| CrCl | calculated creatinine clearance |
| CRF | case report form(s) |
| CRO | contract research organization |
| d4T | stavudine, Zerit® |
| DHHS | Department of Health and Human Services |
| ddI | didanosine, Videx® |
| dL | Deciliter |
| DNA | deoxyribonucleic acid |
| EFV | efavirenz, Sustiva® |
| EIA | enzyme-linked immunosorbent assay |
| FDA | (US) Food and Drug Administration |
| FTC | Emtricitabine |
| g | gram(s) |
| GCP | Good Clinical Practice guidelines |
| HAART | highly active antiretroviral therapy |
| HBV | hepatitis B virus |
| HBsAg | hepatitis B surface antigen |
| HDPE | high‑density polyethylene |
| HIV | human immunodeficiency virus |

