# STUDY DESIGN

This protocol describes a randomized, double-blind, placebo-controlled three-site study to evaluate the safety and tolerability of daily oral TDF among HIV-1 negative MSM.

Four hundred healthy, HIV‑1‑negative MSM will be randomized to one of four treatment arms:

Group 1: TDF 300 mg po QD

Group 2: Placebo po QD

Group 3: No study product for 9 months, followed by TDF 300 mg po QD

Group 4: No study product for 9 months, followed by placebo po QD

Groups 1 and 2 will be referred to as the immediate treatment arms and will receive study product for the entire 24 months of the study. Groups 3 and 4 will be referred to as the delayed treatment arms, and will receive study product starting at 9 months and ending at 24 months, for a total duration of 15 months on study product. For the purposes of this study, a month is considered 30 days. Participants will be stratified by enrollment site.

Participants will be monitored for clinical safety using periodic physical examinations, adverse event reporting, and serial laboratory testing. Given the uncertainty regarding the clinical significance of whole-body duel-energy x-ray absorptiometry [DEXA] findings and their lack of correlation with other clinical data (e.g. fractures), SFDPH site participants will receive DEXA scans at screening and two follow-up visits (at 12 and 24 months in the immediate arm, at 9 and 24 months in the delayed arm), and at the time of study discontinuation, if at least 6 months has passed since the previous scan. Behavioral safety will be primarily assessed by comparing reported risk behaviors between the immediate (pill-groups 1 and 2) and delayed (no pill-groups 3 and 4) treatment arms and will be evaluated by the use of periodic risk behavior assessments via audio computer-assisted self interview (ACASI) and regular laboratory testing for HIV and sexually transmitted infections (STI) including syphilis, *Neisseria gonorrhoeae* (GC), and Chlamydia trachomatis (CT). Additionally, measurements of adherence will be evaluated to determine product acceptability.

Study Schema

R

A

N

D

O

M

I

Z

E

Daily TDF

Daily Placebo

No treatment for 9 months, then daily TDF

No treatment for 9 months, then daily Placebo

Site B

Site A

Site C

Anticipated Timeline

Months

|  | 0-6 | | 7-12 | | | | 13-18 | | | 19-24 | | 25-30 | 31-36 | | 37-42 | |
| --- | --- | --- | --- | --- | --- | --- | --- | --- | --- | --- | --- | --- | --- | --- | --- | --- |

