## Randomization

Participants will be randomly assigned to one of the four arms: immediate study product receipt (TDF or placebo) or delayed study product receipt (TDF or placebo) in a 1:1:1:1 ratio. A CDC statistician will develop the allocation sequence using a permuted blocks randomization scheme. In a block of 8 study numbers, 2 assignments will be to immediate TDF, 2 to immediate placebo, 2 to delayed TDF, and 2 to delayed placebo. Randomization codes will be provided to Gilead Sciences, Inc., and study bottles will be labeled and filled with TDF or placebo using these codes and shipped to the appropriate site. Participants will be randomized to a group only after they have consented to participate and they have met the eligibility requirements for the study. Randomization will be stratified by study site. The list of treatment assignments and the assignment codes will be known only to the statistician and designated individual at Gilead Sciences, Inc., and only CDC will have access to the list of treatment assignments should the need for this information arise.

Group assignments will be concealed in sequentially numbered, sealed envelopes that will be distributed to each site by CDC and maintained in a secure location. After a participant has been properly enrolled in the study, a designated study staff member will obtain the next randomization envelope in sequence and be provided the information indicating the participant’s assignment to a delayed or immediate arm and the randomization number (bottle identification number) assigned.

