## Follow-up Visits

Participants assigned to the immediate treatment arms will be scheduled for follow-up visits at 1 and 3 months after enrollment and then at months 6, 9, 12, 15, 18, 21, and 24 (Table 1, Appendix 3). Study visits for participants assigned to the immediate treatment arm are to be completed + 7 days based on the enrollment visit date. Participants assigned to the delayed treatment arms will be scheduled for follow-up visits at 1 and 3 months after enrollment and then at months 6, 9, 10, 12, 15, 18, 21, and 24 (Table 2, Appendix 3). Study visits for participants assigned to the delayed treatment arm are to be completed + 7 days based on their enrollment visit until their initial dispensing visit . After the initial dispensing visit (month 9), study visits for participants assigned to the delayed treatment arm will be completed + 7 days based on their month 9 visit date. Regularly scheduled evaluations will be made on all participants whether or not they continue to receive study product.

The following procedures are to be performed at all visits unless otherwise specified:

*Epidemiologic/Behavioral Risk Assessment*

- ACASI (3, 6, 9, 12, 15, 18, 21, and 24 months)

Clinical assessment

- Symptom-directed physical examination
- Administration of Adverse Events/Intercurrent Illness Form
- Concomitant Medication Form

*Laboratory assessment:*

- Hematology profile
- Chemistry profile
- Urinalysis
- Blood sample for storage
- Plasma
- Peripheral Blood Mononuclear Cells (PBMCs) (12 months for immediate treatment arms, 21 months for delayed treatment arms only)
- HIV-1 rapid whole blood EIA (3, 6, 9, 12, 15, 18, 21, and 24 months)
- DEXA scan **(SFDPH only: 12 and 24 months for immediate treatment arms, 9 and 24 months for the delayed treatment arms)**
- STI testing
- RPR (12 and 24 months)
- Urine for GC and CT (6, 12, 18, and 24 months)

Standardized HIV risk reduction counseling as per enrollment visit

During the 24 months of the study, additional HIV testing may be requested at any time by study participants, or may be performed as required by the protocol in the case of an indeterminate result or to help determine the timing of HIV infection more precisely.

After participants complete all scheduled study visits, they will be contacted periodically until final study closeout. The purpose of these interim contacts will be to update contact information and to inform participants of the progress of and timeline for completing the study.

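### Scheduled independent safety reviews end at study month 18, before any 24-month result and before roughly 54% to 78% of on-product exposure, depending on accrual

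*Protocol*

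**What the plan says.** Section 10.8 gives the safety review team the task of following clinical and behavioral safety for as long as the study runs, and then fixes its meetings: "The safety review team will convene at scheduled timepoints 6, 12, and 18 months following study initiation". No other section adds a later scheduled review. The Anticipated Timeline in section 3 has a row for safety reviews, but its shading is lost in the text at hand, so it can neither confirm nor exclude later meetings.

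Section 10.8 also provides three routes that carry no end date: rapid review of site safety data by the investigators and CDC, notice of reportable SAEs to the team when the IRBs are told, and ad-hoc meetings. The ad-hoc meetings are triggered by several grade 4 or grade 3 events of the same kind judged probably or definitely related to product. There are no formal stopping rules.

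On duration, the synopsis gives enrollment as "Over 24 months" and follow-up as "24 months for HIV negative MSM, 12 months following HIV diagnosis for MSM who become infected while participating in the study". The Anticipated Timeline ends at month 42, with closeout and analyses among its rows. Under section 3 the immediate arms "will receive study product for the entire 24 months of the study", and the delayed arms start product at month 9 and take it for 15 months. DEXA scans, at the San Francisco site only, fall at "12 and 24 months for immediate treatment arms, 9 and 24 months for the delayed treatment arms" (section 6.8).

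**The concern.** The trial's purpose is extended safety in healthy men, and section 1.4 singles out kidney and bone as systems that may show long-term toxicity. The protocol's own background (Safety, study 903) shows such findings growing with time on drug. Creatinine increases of at least 0.5 mg/dL were seen in 1% of TDF patients at 48 weeks and 3% at 96 weeks. The defined decrease in bone mineral density was met by 6% and then 13% of the TDF arm, against 2% and then 10% of the comparator arm. A review calendar that closes at study month 18 closes before comparable data exist.

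The continuing routes leave a gap in just this area. Section 9.6 takes bone density decreases out of the toxicity grading scale and refers them to section 6.5, which assigns no grade, so they cannot meet a trigger written in grade 3 and 4 events. A grade 1 creatinine rise, which section 9.6 treats as reason to hold product, cannot meet it either. A pattern of such findings by arm would therefore have no set occasion to come before the team after month 18.

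Behavioral safety is affected too. Section 5.2.3 relies on each safety review to compare the delayed arms' risk behavior before and after they start product, and much of the after-product data will not exist by month 18.

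**Working it through.** **Inputs.** Reviews at months 6, 12 and 18 (10.8). Enrollment of 24 months and follow-up of 24 months (synopsis). 400 men, 1:1:1:1 (sections 3 and 5.2), so 200 immediate and 200 delayed. 24 months on product in the immediate arms, and 15 months from participant month 9 in the delayed arms (section 3). Loss of 10-20% (10.3). The protocol gives no accrual pattern; uniform accrual is my assumption.

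**Study length.** 24 + 24 = 48 months on the synopsis, against a timeline that ends at 42. The two do not agree. To fit the timeline, enrollment can last at most 42 - 24 = 18 months, and less once closeout and analyses are allowed for. The surviving column layout of the timeline hints at about 9 months of enrollment. Because table structure may be broken, I use 9 only as the short end of the range.

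**What holds at any accrual speed.** The first man enrolled reaches his month-24 visit about 24 months after study start. Section 6.5 allows 1 month either side for a DEXA scan, which still puts the first 24-month scan near month 23, after month 18. A delayed-arm man can have at most 18 - 9 = 9 of 15 product-months by month 18. His 9-month scan is meant to precede product (6.5), so apart from a scan at discontinuation his only on-product scan is the one at month 24.

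**Exposure before month 18.** Total planned exposure is 200 × 24 + 200 × 15 = 7,800 product-months. For uniform accrual over A months:

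- Immediate arms: (200/A) × 18²/2 if A ≥ 18; 200 × (18 - A/2) if A < 18.
- Delayed arms: (200/A) × 9²/2 if A ≥ 9.

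| A (months) | Immediate | Delayed | Total before month 18 | Share after month 18 |
|---|---|---|---|---|
| 24 | 1,350 | 337.5 | 1,687.5 | 78.4% |
| 18 | 1,800 | 450 | 2,250 | 71.2% |
| 15 | 2,100 | 540 | 2,640 | 66.2% |
| 12 | 2,400 | 675 | 3,075 | 60.6% |
| 9 | 2,700 | 900 | 3,600 | 53.8% |

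As a floor, if all 400 men enrolled on day 1, exposure before month 18 would be 200 × 18 + 200 × 9 = 5,400, leaving 2,400 of 7,800, or 30.8%, after it.

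**Loss to follow-up.** With exponential loss of 10% and 20% over 24 months, the share after month 18 is 77.7% and 77.0% for A = 24, and 52.7% and 51.5% for A = 9. Loss changes little.

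**State of the trial at month 18 under 24-month accrual.** Not yet enrolled: 6/24 = 25%. Delayed-arm men not yet on product: 15/24 = 62.5%. Immediate-arm men who could have reached the month-12 scan: 6/24 = 25%. Under 9-month accrual everyone is enrolled and every delayed-arm man has reached his start date by month 18.

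**The case against.** The strongest reply is that oversight does not lapse. Ad-hoc meetings and reportable-SAE notices have no calendar limit. CDC and the CRO receive every SAE within 24 hours whatever its cause (9.4), and CDC may end the study at any time, including on the team's recommendation (6.14). Bone and kidney findings have participant-level rules throughout (6.5 and 9.6), with chemistry at every visit. Some 9- and 12-month scans from early enrollees will exist by month 18. TDF is a licensed drug with earlier safety studies, which the protocol gives as its reason for having no formal stopping rules.

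Most of this stands. A reader might infer that independent review ends at month 18; the text does not support that, since only the scheduled meetings end. A reader might also infer that the team sees only a narrow set of SAEs, from "All serious adverse events (SAE) that are study related and unexpected will be provided to the safety review team". That sentence does not say it is the whole content: the team also meets to examine the trial's safety results, and section 5.2.3 adds risk behavior. The ad-hoc triggers do not require an event to be unexpected, so clustered grade 3 or 4 renal events judged probably or definitely related would qualify.

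What the reply does not answer is the long-term comparison by arm. Participant-level rules act on one man at a time and do not put accumulating bone or creatinine data before the team. The licensed-drug argument explains the lack of stopping rules, not why meetings should stop before the 24-month data.

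**Conclusion.** The point holds as a gap in scheduled review. That no 24-month visit or 24-month scan, and no more than 9 of a delayed-arm man's 15 product-months, can reach a scheduled meeting follows from the protocol's own dates and needs no accrual assumption.

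The share of exposure does need one. It is 78% only with uniform accrual over the synopsis's 24 months. It is 54% to 71% for the 9 to 18 months considered in order to fit the timeline, all without loss. Neither 78% nor a 48-month trial should be read as a settled fact, because the synopsis and the timeline disagree. That disagreement does not show how the review schedule came to be written. This is a worthwhile, inexpensive improvement to the safety plan, not evidence that the men would go unmonitored.

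**What to change.** Amend section 10.8 so that scheduled reviews continue, for example every 6 months, until the last participant completes month 24. State that the reports for these meetings include renal and DEXA summaries by arm. Reconcile the 24-month enrollment in the synopsis with the 42-month Anticipated Timeline, so that the number of reviews follows from one agreed duration.

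The cost is protocol wording plus a few more meetings and reports for the existing team: about four or five on 24-month accrual (months 24, 30, 36, 42 and possibly 48), and fewer if the timeline is the intended duration. No change to sample size, visits or assessments is needed.

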## Serious Adverse Event Reporting Requirements

All Serious Adverse Events

The CRO and CDC must be notified within 24 hours regarding the occurrence of any SAE that occurs after the start of study. SAEs may first be reported via telephone or fax. The procedures for reporting all SAEs, regardless of causal relationship, are as follows:

Record the SAE on the AE CRF and complete the “Serious Adverse Event Report” form.

- Fax the serious adverse event report to both the CRO and CDC within 24 hours of the investigator’s knowledge of the event.
- For fatal or life‑threatening events, also fax copies of hospital case reports, autopsy reports, and other documents when requested and applicable.

| CRO Medical Monitor: | [name]  Phone: [contact]  [contact]/ [contact] Fax: Constella Group, Inc.  Attn: [name]/[name]  [contact] E-mail: [[contact]](mailto:[contact])  [[contact]](mailto:[contact]) |
| --- | --- |
| CDC Medical Officer: | [name], MPH  Phone: [name]/ [contact] Fax: [contact]  [name]/[name] E-mail: [contact] |

CDC may request additional information from the investigator to ensure the timely completion of accurate safety reports.

The investigator should identify all therapeutic measures necessary for resolution of the SAE. Any medications necessary for treatment of the SAE must be recorded onto the concomitant medication section of the participant’s CRF.

Preliminary reports of deaths, life-threatening, or serious and unexpected AEs will be followed by detailed descriptions on the SAE CRF and will include copies of hospitalization summaries, pathology reports, operative reports, laboratory reports, autopsy reports and/or other documents when applicable. Follow‑up of ongoing SAEs and clinically significant AEs that are possibly or probably related to study product will continue up to 30 days after study product discontinuation or until the site investigator and/or CDC’s medical officer determine that the participant’s condition is stable, whichever is longer. CDC may request that certain adverse events be followed until resolution.

Post-Study Reporting Requirements

All deaths, regardless of cause or relationship, must be reported for participants on study and for deaths occurring within 30 days of last study product dose or within 30 days of last study evaluation, whichever is longer.

Investigator Reporting Requirements for SAEs

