A SAE may qualify for reporting to regulatory authorities if the SAE is possibly attributable to the study drug, and is unexpected/unlisted based upon the current Investigator’s Brochure. In this case, all investigators will receive a formal notification describing the SAE.

The site principal investigator should notify their local Institutional Review Board (IRB) in accordance with the local institutional policy.

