## Safety Analyses for Clinical and Laboratory Measurements

The rate of severe reactions will be used as the primary measure of clinical safety of this study drug. Assessment of product safety will include clinical observation and monitoring of hematologic and chemical parameters. All participants will be monitored for local and systemic adverse reactions during the course of the trial. Participants will be closely monitored for the first 8 weeks after product dispensation and followed for at least 15 months on product.

Adverse experiences will be coded into MedDRA (Medical Dictionary for Regulatory Activities) preferred terms. The number and percentage of participants experiencing each specific adverse experience will be tabulated by severity and relationship to treatment. Overall summaries by treatment will include the number and percentage of participants experiencing: (1) an adverse experience; (2) any moderate, severe, or life-threatening experience; (3) any severe or life-threatening experience; (4) adverse experience judged possibly related, probably related, or definitely related to treatment. Additional summaries will summarize the effect of adverse events on study drug dosing. A separate tabulation of SAEs will also be generated and will provide details including severity, relationship to treatment, onset, duration, and outcome. Adverse events that lead to product or study discontinuation will be listed separately.

Participants who become HIV-1 infected while on study will be monitored in a second part of the protocol (Part B). Both potential benefits and potential detrimental effects of the study product based on secondary endpoint analyses described above will be investigated. Clinical endpoints (major and minor) associated with the disease progression (e.g., setpoint, resistance,) will be recorded. Because few clinical endpoints are expected to be observed to support a quantitative analysis, qualitative case-descriptions will be done.

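### The SAE clause for the scheduled safety reviews (10.8) is narrower than the review team's own remit and than the protocol's all-SAE reporting and tabulation

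*Protocol*

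**What the plan says.** Section 10.8 opens with a broad remit: "A safety review team will review the progress and clinical and behavioral safety profile of this study while the study is ongoing". Meetings are set for 6, 12 and 18 months after study initiation, "to examine the safety results of the trial" and to look at conduct issues such as accrual and data quality.

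The next paragraph deals with SAEs. For the scheduled meetings it says "All serious adverse events (SAE) that are study related and unexpected will be provided to the safety review team at their regular safety reviews". The same sentence adds a faster route: "should any reportable SAEs occur, these will be reported to the safety review team at the same time as they are reported to the IRBs".

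The section then declines to set formal stopping rules. Ad-hoc meetings are triggered by repeated events, for example "> two grade 4 adverse events of the same nature", where these are definitely or probably related to product. A similar trigger covers grade 3 events. At scheduled and ad-hoc reviews alike, the team makes a clinical assessment of whether the kind, frequency and severity of adverse effects call for early termination.

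Other sections do not filter SAEs:

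- 9.4, on site reporting to the CRO and the sponsor: "The procedures for reporting all SAEs, regardless of causal relationship, are as follows". Notification is due within 24 hours.
- 10.5, on analysis: "A separate tabulation of SAEs will also be generated", with relationship to treatment as one of the details given for each event.
- 10.3, on sample size: the safety calculations concern the ability to detect SAEs, with no condition on relatedness or expectedness.

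Section 9.4 also shows what unexpected means. An SAE may qualify for regulatory reporting if it "is possibly attributable to the study drug, and is unexpected/unlisted" by reference to the current Investigator's Brochure.

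**The concern.** The one sentence that specifies the SAE content of the scheduled reviews sets two conditions, both of which must be met. Each can remove events that matter to a safety monitor.

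Relatedness is an investigator's case-by-case judgment (9.6), made blind to assignment. Under that scale an event attributed to another cause is unrelated. An excess of such events on one arm shows up only when all of them are counted by arm, which is what a placebo control makes possible.

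Expectedness removes events that are already listed. The Clinical Experience section of the Introduction describes renal failure, renal tubular dysfunction with Fanconi's syndrome, and lactic acidosis in patients taking TDF. The Rationale section singles out kidney and bone for close monitoring. If such events are listed in the Brochure, they fail the filter even when judged related.

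Because there are no formal stopping rules, the team depends on what it is given. Frequency is hard to judge from a filtered count. The team's recommendation is also one of the listed grounds for terminating the study (6.14).

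**Working it through.** This is mainly a comparison of texts. One figure in the plan bears on it.

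**1. Which SAEs does the safety planning count?** Section 10.3 states that at a true SAE rate of 3% the probability of five or more events is 18.2% with n = 100 and 71.9% with n = 200. Treating every SAE as countable:

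P(X ≥ 5), X ~ Binomial(100, 0.03) = 0.1821

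P(X ≥ 5), X ~ Binomial(200, 0.03) = 0.7190

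Both agree with the plan. The planning figures rest on a plain SAE rate with no relatedness or expectedness factor.

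**2. The SAE sets side by side.**

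| Use | SAEs covered | Section |
|---|---|---|
| Site to CRO and sponsor, within 24 hours | All, any causality | 9.4 |
| Tabulation in the analysis | All, relationship shown | 10.5 |
| Safety sample size | All | 10.3 |
| Scheduled safety reviews | Study related and unexpected | 10.8 |
| Faster route to the team | Reportable, when the IRBs are told | 10.8 |
| Ad-hoc triggers | Repeated grade 3 or 4 events of the same nature, probably or definitely related, any expectedness | 10.8 |

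**3. Which SAEs have no stated route to a scheduled review?** Take the four combinations of relationship and expectedness:

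- Related and unexpected: covered by the SAE clause.
- Related and expected: not covered by the clause. They can prompt an ad-hoc meeting if they are grade 3 or 4, repeated, of the same nature, and probably or definitely related. A single event, or events judged only possibly related, would not.
- Unrelated, whether expected or unexpected (two combinations): not covered by the clause or by the triggers.

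The reportable-SAE route may pick up some of the last three combinations. Section 10.8 does not define reportable. Section 9.4 leaves IRB notification to local institutional policy, and its own regulatory criterion is again possible attribution plus unexpectedness. A complete SAE listing is not assured by this route.

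**4. Do the two conditions work together?** In 9.6, one ground for calling an event definitely related is that it is a known reaction to the product. In 9.4, unexpected means unlisted. An event attributed to TDF because it is a known reaction is more likely to be a listed one. The conditions therefore pull against each other for the toxicities already under suspicion.

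**5. Can the gap be sized?** Not from the documents. They give no share of SAEs expected to be both related and unexpected. The 200-participant figures also do not describe any scheduled review. Enrollment runs over 24 months, the delayed arms start product at month 9, and the last scheduled review is at month 18. Assuming uniform accrual of 100 men per arm from study initiation, the number who have started TDF by month 18 is

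100 × 18/24 + 100 × (18 − 9)/24 = 75 + 37.5 ≈ 112.

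By month 12 it is 50 + 12.5 ≈ 62, and by month 6 it is 25. No percentage is therefore attached to this point.

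**The case against.** The strongest reply is that 10.8 never says the team receives nothing else. It gives the team the whole safety profile to review and has it examine the trial's safety results. It also asks for a judgment on frequency, which related and unexpected cases alone could not support. On this reading the SAE sentence is a minimum for individual case reports, on top of the general safety results. The section on self-unblinding supports it, since it sends risk-behavior data to each safety review. This stands: a reader might infer that the team is given only the filtered SAEs, or that an excess of expected toxicities would be hidden from it, and the document supports neither.

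The second reply is that the renal example has another route. The ad-hoc triggers ignore expectedness, and being a known reaction pushes an event towards the definitely related category. Repeated, probably or definitely related renal events of grade 3 or 4 would convene the team. This also stands, within the limits set out in the working.

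Third, whether renal failure or lactic acidosis counts as expected depends on the Brochure, which is an appendix not shown. The Introduction is background narrative and notes other possible contributors in many of the renal cases and in both lactic acidosis cases. So the example is a possibility, not a finding.

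Fourth, the sponsor is told of every SAE, reviews safety data rapidly, and may stop the study over the incidence or severity of adverse events. The gap concerns what one body is promised, not oversight of the trial as a whole.

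What remains is that the general remit does not say which SAEs are supplied, and the one sentence that does is narrow. If the full set is meant, that sentence misstates it.

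**Conclusion.** The point holds in a limited form. The SAE clause in 10.8 is narrower than the remit in the same section and narrower than the reporting in 9.4 and the tabulation in 10.5. SAEs judged unrelated, or related but listed, are not assured to reach the scheduled reviews. Some will reach the team as reportable SAEs or through the ad-hoc triggers, and others may be included in the safety results it examines.

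The size is one inconsistent sentence, with a real but unquantified effect on safety oversight. The conclusion rests on the text of 10.8, 9.4, 9.6 and 10.5. It does not depend on whether any particular event is in the Brochure or on any assumed share of SAEs passing the filter. It corrects a stated rule and is not a request for detail that a statistical analysis plan would normally supply.

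**What to change.** Amend the SAE sentence in 10.8 so that all SAEs, regardless of relationship or expectedness, are supplied at each scheduled review. Tabulate them by masked arm, with relationship and expectedness shown as columns. Leave the reportable-SAE route and the ad-hoc triggers as they are.

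The cost is one sentence in the protocol and one table per scheduled review. The sponsor and the CRO are already notified of every SAE within 24 hours, and the sponsor's statistician already holds the assignment list needed for a coded-arm table. No new data collection from sites is needed, apart from recording expectedness against the Brochure for any SAE where this has not been done. No clinical management rule changes.
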